**Fig. 1 Fig1:**
[figure not shown]
CONSORT participant flow diagram throughout the trial

### Intervention

To develop the intervention, we conducted a three-phase Delphi study. During the Delphi procedures, we established expert opinions on and a critical assessment of the content of the smoking cessation intervention. The finalised KISMET intervention concept entails the following three core components: (1) behavioural counselling (based on the principles of CBT and motivational interviewing); (2) pharmacological treatment (nicotine replacement therapy and other medication); and (3) peer support. Based on the outcomes of the Delphi study, we defined the content and structure of these three core components as well as strategies for optimal implementation, such as frequency, duration, dose, responsibilities of MHCPs, and other organisational aspects. The details of the Delphi study are described elsewhere [36].

#### Core components

*Behavioural counselling* will be delivered in groups to create group cohesion and support as well as to reduce the time investment of the FACT teams. Additionally, patients will be offered individual consultations according to their specific needs. They will initially receive psychoeducation about the basic mechanisms of nicotine addiction and what smoking cessation and withdrawal might entail physically and mentally. The information will be comprehensible and facilitated by a personal workbook. An essential part of the psychoeducation will be the normalisation of relapse and lapses to ensure that they are not labelled as failures. This will promote a flexible approach to smoking cessation as a nonlinear process, where (re) lapses are events that can occur in the process of quitting.

These aspects will be addressed in consideration of participants’ psychiatric conditions and their interactions with smoking (cessation). The underlying function and meaning assigned by the patient to smoking will serve as the starting point for finding alternative ways for regulating negative emotions and handling stressful situations *independently.* This notion directly opposes *dependence* on nicotine. Next to learning new coping mechanisms for burdensome emotions, the group sessions will also focus on the influence of smoking on psychotic symptoms, such as hearing voices, and the role of smoking in dealing with these experiences.

The behavioural support will be aimed at helping patients to recognise, accept, and deal with physical, mental, and emotional withdrawal symptoms. Furthermore, personalised relapse prevention plans with self-management techniques will aid in preparing patients for moments in which they anticipate finding themselves vulnerable to relapse.2.*Pharmacological treatment* is recommended for all patients. The MHCPs will discuss the advantages and disadvantages of pharmacological treatment. The patient and clinician will jointly decide on medication intake based on the patient’s preferences and possible intolerances as well as the clinician’s professional knowledge. The medication choices are nicotine replacement therapy (NRT), varenicline, or bupropion, among which NRT and varenicline are the preferred choices. Doses, possible side effects, and interactions with other medication are well protocoled and based on national and international guidelines [37, 38]. A physician/psychiatrist or clinical nurse specialist will supervise medication use and regularly check in with the patient. Special attention will be paid to patients who take antipsychotic medication, such as Clozapine, as doses are adjusted for people who smoke [39]. Hence, a patient’s plasma levels of Clozapine might rise following smoking cessation, and thus, reducing medication doses by 30% is recommended [40].3.*Peer support* group meetings will occur on a weekly basis and be facilitated by an expert-by-experience. The expert-by-experience will be a person who has personal experience of addiction, preferably smoking, and will in some cases also have personal experience with SMI. The group meetings will always follow the same structure: first, experiences during past week will be reflected on and exchanged in pairs and plenary, and second, specific topics chosen by the participants will be discussed. The expert-by-experience will play a facilitating and supporting role by sharing their experiential knowledge. The main goal will be to foster patients’ autonomy and self-management.

### Usual care

FACT teams in the control condition will not receive any training and will provide usual care. Thus, people with SMI will have unrestricted access to mental health care and treatment for smoking cessation according to current national guidelines [37]. Furthermore, they will not be allowed to participate in a structured smoking cessation programme for the duration of the study. In case of positive outcomes of this intervention study, control group participants will be offered support to quit smoking in line with the KISMET intervention.

### Training of MHCPs

The KISMET intervention will be provided by trained mental health care workers. Two MHCPs (mental health nurses, clinical nurse specialists, and experts-by-experience) from FACT teams assigned to the intervention condition will participate in a one-day training session. They will function as role models for their colleagues within the FACT team as well as their patients on the subject of smoking cessation and will guide the group sessions. The training will consist of the following: (a) education about pharmacological treatment for smoking cessation, including its effectiveness and possible side and interaction effects; (b) CBT techniques; (c) motivational interviewing techniques; (d) psychoeducation about the connection between SMI, mental health, and tobacco addiction; and (e) principles of peer support. Furthermore, information will be provided about the study design and measurement of the study parameters. The training will be set up and provided by three highly experienced trainers with ample expertise on smoking cessation and mental health. The FACT teams can decide which health care workers will be trained for the intervention. This will promote a greater resemblance to general care as well as enhance the generalisability of the study.

### Main outcome measures

#### Primary outcome

##### Smoking

The primary outcome parameter is smoking behaviour at 12 months. This outcome is defined by exhaled carbon monoxide (CO) measured with a CO monitor and self-report. We define smoking cessation as a CO reading of less than 10 ppm (ppm).

Smoking history and current smoking status will be assessed through a short questionnaire.

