**Methods:**

A pragmatic, cluster-randomised controlled trial with embedded process evaluation will be conducted. Randomisation will be performed at the level of FACT teams, which will be assigned to the KISMET intervention or a control group (care as usual). The intervention will include pharmacological treatment combined with behavioural counselling and peer support provided by trained mental health care professionals. The intervention was developed using a Delphi study, through which a consensus was reached on the core elements of the intervention. We aim to include a total of 318 people with SMI (aged 18–65 years) who smoke and desire to quit smoking. The primary outcome is smoking status, as verified by carbon monoxide measurements and self-report. The secondary outcomes are depression and anxiety, psychotic symptoms, physical fitness, cardiovascular risks, substance use, quality of life, and health-related self-efficacy at 12 months. Alongside the trial, a qualitative process evaluation will be conducted to evaluate the barriers to and facilitators of its implementation as well as the satisfaction and experiences of both patients and mental health care professionals.

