### Participants

Participants will be people with SMI who receive treatment from FACT teams. Patients who fulfil the following criteria will be eligible for inclusion:Fulfils the criteria of SMI according to Delespaul and the SMI Consensus Group, which are defined as follows [34]: presenting a non-transient (structural or long-term for several years) psychiatric disorder, for which coordinated care from a care network is necessary and which is not in symptomatic remission; presenting severely impaired social and/or occupational functioning which is not in functional remission;Aged ≥18 years;Current smoker (≥ 5 cigarettes) without a quit attempt in the past month;Expresses an interest in stopping / cutting down smoking;Willing and able to sign informed consent.

Patients who are pregnant or breastfeeding, have severe cognitive impairments, present a primary diagnosis of substance use disorder (with the exception of cannabis use disorder), or are experiencing an acute psychiatric crisis or acute physical disease at the time of inclusion will not be eligible to participate.

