##### Nicotine dependence

The degree of nicotine dependence will be measured with the Fagerström Test for Nicotine Dependence (FTND) [41]. This self-report questionnaire contains six items. The *yes/no* items are scored 0 or 1, while the multiple-choice items are scored from 0 to 3. The subscores are added to yield a total score between 0 and 10, indicating low, moderate, or high dependence.

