### Statistical analysis

The characteristics of people with SMI in the intervention and control groups will first be presented at baseline and using descriptive statistics (mean [standard deviation], median [range], or frequencies [percentage]). All analyses will be conducted on an intention-to-treat basis, including all randomised patients in the groups to which they were allocated where data are available.

To compare the effects of the intervention with those of usual care on CO-verified smoking cessation (primary outcome) between baseline and 3, 6, and 12 months, a mixed model with a three-level structure (observations clustered within patients, patients clustered within FACT teams, and FACT teams clustered within institutions) will be used, including a random intercept the patient, FACT team, and institution levels [52]. The necessity of random slopes will be assessed using the likelihood ratio test, which will compare the model with random intercepts with a model with random intercepts and random slopes.

The first model will be an ‘overall’ model, with only the treatment variable included. This will provide information about the treatment effect of the primary outcome (odds ratio, 95% confidence interval, and *p*-value), which can be interpreted as the average overall treatment effect over time. Subsequent analyses will include a categorical variable for time (as a dummy variable) as well as an interaction between treatment and time to enable an in-depth investigation of the intervention’s effects at different time points [52].

For binary secondary outcome variables, a similar analysis strategy to the one above will be used. For continuous variables, we will run the first model as mentioned as well as use a longitudinal analysis of covariance to appropriately adjust for the baseline value of the outcome variable [53].

All of the aforementioned models will be additionally adjusted for prognostic variables to increase the precision of the crude treatment effects [54]. These prognostic variables will be identified through a literature study and directed acyclic graphs (DAGs) [55].

Finally, a descriptive analysis will be performed to compare the number of cigarettes smoked per day over time between the two groups as well as attendance at group sessions within the intervention group.

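### The primary outcome is said to rest on CO and self-report, but the sentence defining cessation uses CO alone and gives no rule for people who report smoking yet read below 10 ppm

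*Protocol article*

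**What the plan says.** Four places in the protocol article bear on the endpoint.

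- **Abstract, Methods:** "The primary outcome is smoking status, as verified by carbon monoxide measurements and self-report".
- **Primary outcome, Smoking:** first "This outcome is defined by exhaled carbon monoxide (CO) measured with a CO monitor and self-report", then the operative rule, "We define smoking cessation as a CO reading of less than 10 ppm". A separate line adds "Smoking history and current smoking status will be assessed through a short questionnaire", without linking the questionnaire to the rule.
- **Statistical analysis:** the modelled quantity is "CO-verified smoking cessation (primary outcome) between baseline and 3, 6, and 12 months". Self-report is not mentioned.
- **Table 1:** current smoking status, use of combustible cigarettes and CO are all recorded at baseline, 3, 6 and 12 months.

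The Participants section admits a "Current smoker (≥ 5 cigarettes) without a quit attempt in the past month", gives no period for the cigarette count and sets no minimum CO. It accepts an interest in cutting down as well as in stopping. The Sample size section is built on abstinence rates of 30% and 15%.

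**The concern.** The description of the outcome has two components and the definition of cessation has one. For a participant whose report and CO agree, this makes no difference. For one who reports smoking and reads below 10 ppm, the description points to smoker and the definition to quitter. Two analysts could each follow the section and code that person differently.

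Such participants are plausible here, because people aiming only to reduce are eligible and cutting down is a realistic result. Two consequences are possible. If continuing smokers fall below the cut-off equally often in both arms, the contrast in true abstinence is diluted. If the intervention makes people smoke less without stopping, they may fall below it more often in the intervention arm, and a difference appears that is not abstinence. Patients and teams are not blinded, so the coding of discordant cases should be fixed before outcome data are seen.

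**Working it through.** **1. The plan's own figure.** Inputs from Sample size: 30% and 15%. Alpha and power are not stated; I assume 0.05 two-sided and 80%. The normal-approximation formula without continuity correction is

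n = [1.960 × √(2 × p̄ × (1 − p̄)) + 0.842 × √(p₁(1 − p₁) + p₂(1 − p₂))]² / (p₁ − p₂)²

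With p̄ = 0.225, this is [1.960 × √0.34875 + 0.842 × √0.3375]² / 0.0225 ≈ 120.5, which rounds up to the stated 121 per group. The figure is reproduced and is not in dispute.

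**2. Equal misclassification.** Let f be the share of continuing smokers reading below 10 ppm, the same in both arms. The article gives no value, so f is an assumed range. Every true abstainer is taken to read below 10 ppm. Under the literal CO rule the apparent rate is p + f(1 − p), and the difference is (1 − f) × 15 points.

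| f | Intervention | Usual care | Difference (points) | Odds ratio | Power at 121 per arm |
|---|---|---|---|---|---|
| 0 | 30.0% | 15.0% | 15.0 | 2.43 | 80% |
| 5% | 33.5% | 19.3% | 14.3 | 2.11 | 71% |
| 10% | 37.0% | 23.5% | 13.5 | 1.91 | 63% |
| 20% | 44.0% | 32.0% | 12.0 | 1.67 | 49% |

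For example, at f = 10%: 0.30 + 0.10 × 0.70 = 0.370 and 0.15 + 0.10 × 0.85 = 0.235.

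**3. Unequal misclassification.** Suppose there is no true effect (15% abstinent in both arms), with f = 20% under the intervention and 10% under usual care, both assumed. The apparent rates are 0.15 + 0.20 × 0.85 = 32.0% and 0.15 + 0.10 × 0.85 = 23.5%. That is a false difference of 8.5 points, with about a 31% chance of significance at 121 per arm.

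The power figures treat participants as independent. The trial is clustered and uses a repeated-measures mixed model, so they show the direction and rough scale of the effect and are not this trial's power.

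**The case against.** The strongest reply is that the sentences should be read together. On that reading, 10 ppm is the cut-off for the CO component, applied to people who say they have stopped. The Abstract names both sources, and the term CO-verified in the analysis section presupposes a claim to verify. This reading is coherent and may be what the authors intend. It stands against any statement that the trial has adopted a CO-only endpoint, but it does not supply the missing rule, because nowhere is the combination or the handling of discordant cases written down.

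Other limits also stand.

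- The misclassification shares are assumptions.
- The 30% and 15% come from earlier trials whose endpoint definitions cannot be seen here. If those used CO in the same way, some misclassification is already in the planning rates.
- The article condenses a fuller protocol, so the absence of an abstinence window is not in itself an error.
- Arguments from how fast CO clears, or from cannabis smoke raising it, rest on facts outside the article. The point needs neither.

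A reader might also infer two primary outcomes sharing one alpha, because the Fagerström test of nicotine dependence sits under the primary outcome heading. The text does not support this. That section names a single primary parameter, the sample size is based on abstinence only, and the analysis section labels cessation as the primary outcome. The placement is a matter of headings.

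**Conclusion.** The point holds as an internal inconsistency in the definition of the primary endpoint. The outcome is described as CO and self-report, cessation is defined by CO below 10 ppm, and the discordant case is left without a rule. Taken literally, the definition counts some continuing smokers as quitters in a trial planned on abstinence.

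The size is unknown from the article. With an assumed 5% to 20% of continuing smokers below the cut-off in both arms, and clustering ignored, the 15-point difference becomes 14.3 to 12.0 points. With unequal shares the error can run towards a false benefit, so the net direction is not established. It would go too far to conclude that light smokers will be counted as quitters in the analysis, or that power will fall to the tabulated values.

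**What to change.** Reconcile the two sentences under Primary outcome and carry the same wording into the Abstract and Statistical analysis. Define cessation at each assessment (3, 6 and 12 months, with 12 months as the primary time point) as self-reported tobacco abstinence over a pre-specified window **and** CO below 10 ppm. State that any self-reported smoking, or a CO of 10 ppm or more, counts as smoking.

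Optionally, add a sensitivity analysis for self-reported tobacco abstainers with CO of 10 ppm or more who report smoking cannabis. Cannabis use disorder is not an exclusion ("with the exception of cannabis use disorder"), and the cannabis questionnaire is scheduled at 6 and 12 months, though not at 3.

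The cost is mainly wording. Smoking status, cigarette use and CO are already collected at every visit; at most, the short questionnaire must ask about the chosen window. The 121 per group is unaffected, because 30% and 15% are stated as abstinence rates. The downside is slightly lower observed abstinence than under CO alone.

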##### Nicotine dependence

The degree of nicotine dependence will be measured with the Fagerström Test for Nicotine Dependence (FTND) [41]. This self-report questionnaire contains six items. The *yes/no* items are scored 0 or 1, while the multiple-choice items are scored from 0 to 3. The subscores are added to yield a total score between 0 and 10, indicating low, moderate, or high dependence.

### Secondary outcomes

#### Physical health

##### Body mass index (BMI)

BMI will be computed as follows: bodyweight (kg) divided by the square of height (cm). Body weight will be measured with a scale, while height will be measured with a tape measure.

##### Physical fitness

Physical fitness will be assessed using the 6-minute walk test [42], which was demonstrated to be feasible among people with SMI [43]. In this test, the distance covered by the patient in 6 minutes at a normal walking pace is registered.

##### Systolic and diastolic blood pressure

Blood pressure is defined in mmHg and will be measured twice in a seated position with legs uncrossed after at least 5 minutes of rest. The average of both measurements will be recorded.

##### Lipid profile and glucose metabolism

Serum LDL, HDL, total cholesterol, triglycerides, and fasting plasma glucose metabolism will be measured using venepuncture at the laboratories patients visit for their annual check-ups. All lab measurements will be collected after overnight fasting (8–12 hours). For these measurements, two 7-mL blood samples will be collected (one 4-mL EDTA sample and one 3-mL heparin blood sample).

In case of abnormal blood pressure or blood values, the patient’s general practitioner or coordinating MHCP will be contacted.

#### Patient reports

##### Symptoms of depression and anxiety

Symptoms of depression and anxiety will be measured using the 14-item Hospital Anxiety and Depression Scale (HADS) over the past 4 weeks [44]. This questionnaire consists of 14 items, of which seven items rate anxiety and seven items rate depression. The patient is asked to rate their agreement or disagreement on a 4-point scale. For example, item 13 is ‘I get sudden feelings of panic’ and item 2 is ‘I still enjoy the things I used to enjoy’.

##### Psychotic symptoms

We will assess the severity of psychotic symptoms using the six-item Positive and Negative Syndrome Scales (PANSS-6). The PANSS-6, a shorter version of the original 30-item PANSS, contains only six items and is therefore more feasible [45]. This version is a validated compilation of three negative symptoms (N1 – Blunted affect, N4 – Social withdrawal, and N6 – Lack of spontaneity and flow of conversation) and three positive symptoms (P1 – Delusions, P2 – Conceptual disorganisation, and P3 – Hallucinations). The PANSS-6 will be scored by the MHCP who knows the patient best.

##### Substance use

The use of alcohol, nicotine, and other substances will be measured using the World Health Organization Alcohol, Smoking and Substance Involvement Screening Test (WHO-ASSIST) [46]. This eight-item screening test assesses lifetime and 3-month involvement, dependence, preoccupation with and negative consequences of substance use.

##### Cannabis questionnaire

Cannabis use will be assessed using a self-report questionnaire that contains seven questions regarding frequency, consumption history, quantity, and means of consumption.

##### Health-related self-efficacy

The Patient Activation Measure (PAM-13) is a reliable questionnaire that contains 13 items, which are derived from the original PAM-22 [47]. The questionnaire assesses patients’ self-reported knowledge, skills, and confidence in health-related self-efficacy.

##### Quality of life

Quality of life will be measured using the Short Form-12 (SF-12) questionnaire. The SF-12 is a generic, reliable, and validated instrument that comprises 12 items, which are derived from the SF-36 questionnaire [48]. The physical and mental component summary scores of the SF-12 will be used. Dutch age- and sex-standardised population norms are available [49].

##### Physical activity

Self-reported physical activity will be recorded on each of the four assessments. The frequency per week and impact level of physical activity (low-impact, medium-impact, or strenuous) will be registered.

#### Demographics

Demographic data (i.e., age, gender, educational level, marital status, employment status, diagnosis of SMI, number of years receiving mental health care, and data about past and current medication use) will be collected directly from patient records.

#### Other

*Attendance* at group sessions and peer support group meetings will be registered by the MHCPs delivering the group sessions. *Serious adverse events* will be registered continuously.

Table 1 presents an overview of all outcome measures at each time point:

**Table 1 Tab1:** Outcome measurements, instruments and data collection schedule

	Baseline	3	6	12
